#### International caries detection and measurement system (ICDAS)

2.8.1

ICDAS is a caries measurement system that uses the visual method to detect caries. It can measure carious lesions at the subclinical stage; ICDAS considers coloration changes sufficient to identify lesions in the incipient stages and does not recommend the use of explorers.

This measurement system examines five surfaces and uses codes that range from 0 to 6, depending on the severity of the injury, where 0 indicates a healthy surface.^[33–35]^ This system also evaluates the condition of the surface in terms of restorations, where it uses codes that range from 0 to 8, depending on the type of restoration used.^[33–35]^ For this study, the examiners will be calibrated and previously standardized (Kappa > 0.80).

### Estimation of costs

2.9

The estimation of the costs of the interventions will be from the perspective of the service provider, i.e., all the human and material inputs necessary for the implementation of these two interventions will be identified and included. The unit and average cost of each one of the interventions will be estimated in the same evaluation periods; afterward, it will be determined which of the two interventions is more cost-effective for reducing the incidence of caries.

The cost estimate will include costs related to the training of the personnel that will apply each of the technologies, number of people needed for the application, salaries, and application time, number of control reviews, as well as the costs of purchasing the material and instruments.

### Sample size

2.10

The sample size was calculated using a formula for the difference of proportions. The proportions used in this calculation were the decreases in incidence reported with the use of fluoride varnish (60%) and PFS (40%), a power of 80%, and an α of 95%, which gave a sample size of 97 subjects. In the end, 15% more subjects were added due to the losses to follow-up reported in longitudinal studies, which amounted to 114 subjects for each group.

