**Material and methods::**

This is a randomized experimental design. Participants will be assigned to two treatment groups of 114 each. In the first group, pit and fissure sealants will be applied, whereas the second group will receive a fluoride varnish. The work will be carried out in schoolchildren that attend public elementary schools in the state of Hidalgo, Mexico. The result variable will be the incidence of caries and the total cost of each of the interventions will be calculated in order to calculate the intervention's cost-effectiveness.

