## Introduction

1

Dental caries is one of the most frequently encountered oral health problems worldwide. Official figures report that between 60% and 90% of children worldwide suffer from dental caries and that caries occur mainly among the most socioeconomically disadvantaged populations.^[1]^ It affects different spheres of people's lives and has a negative impact on people's quality of life, which is why it is considered a public health problem.^[2]^ Dental caries is a demineralization process of the hard tissues of the tooth, which generates a softening of the surface and subsurface of the enamel that, if it is not stopped, can generate a cavity and even cause the loss of the dental organ.^[3]^ One of the areas most affected by dental caries are the pits and fissures of the occlusal surfaces^[4,5]^; according to some researchers, these pits and fissures account for about 90% of all caries cases due to the presence of deep and narrow pits and fissures.^[6,7]^ Several studies indicate that occlusal surfaces are more susceptible to decay than smooth surfaces due to a lack of post-eruptive maturation and reduced mineral content.^[6–8]^

Concepts on the management of carious lesions have changed during the last few decades.^[9–11]^ Increasing knowledge about the importance of preventive dentistry and the management of incipient lesions has modified the dentist's typical protocols, specifically by promoting the current focus on less invasive treatments and trying to preserve the greatest amount of enamel for as long as possible.^[9–11]^ Topical fluorides, in their different forms (dentifrices, mouth rinses, gels, and varnishes), allow a local protective effect to be generated on the tooth surface by increasing the exposure time between the fluoride and tooth enamel.^[12,13]^ This increased exposure helps facilitate the remineralization process, which decreases the appearance of new carious lesions in the areas where it is applied. The use of fluorides contributes significantly to the prevention and management of carious lesions.^[12]^ Also, the evolution of dental materials enabled the improvement of preventive methods in dentistry, e.g., the changes in and new types of resins and their application, from the technique of acid etching introduced by Buonocore in 1955 and the development of acrylic resins by Bowen in 1953 to the materials that we know today.

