### Measuring the effectiveness of the intervention

2.8

The primary results for this project are the incidence of caries at 6, 12, 18, and 24 months between the sealant and varnish groups.

The incidence of dental caries considers the measurement of the existence (or not) of visible changes in the surface of the enamel compared to the basal measurement. In the clinical evaluation, visual caries detection and a standardized and international caries measurement system, known as International Caries Detection and Measurement System (ICDAS), will be used.

The reviews will occur every 6 months for a 24-month period.

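### The sample size enters reported decreases in incidence (60% and 40%) as if they were arm incidences, so the stated 80% power is not tied to the primary outcome

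*Protocol article*

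**What the plan says.** Section 2.10 (Sample size) describes the method: "The sample size was calculated using a formula for the difference of proportions". It names the inputs: "The proportions used in this calculation were the decreases in incidence reported with the use of fluoride varnish (60%) and PFS (40"%). It then gives the error rates and the result: "a power of 80%, and an α of 95%, which gave a sample size of 97 subjects". The allowance for losses follows: "15% more subjects were added due to the losses to follow-up reported in longitudinal studies, which amounted to 114 subjects for each group". The abstract repeats the final size: "Participants will be assigned to two treatment groups of 114 each".

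Section 2.8 fixes the outcome: "The primary results for this project are the incidence of caries at 6, 12, 18, and 24 months between the sealant and varnish groups".

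The article gives no untreated incidence and no expected incidence in either arm. The nearest figure is in the Introduction: "between 60% and 90% of children worldwide suffer from dental caries". That is a worldwide frequency of the disease. It is not a 24-month incidence on first molars that were sound at entry.

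**The concern.** A difference-of-proportions formula needs the proportion with the outcome expected in each arm. Here the outcome is new caries, so the inputs should be two caries incidences. Section 2.10 instead describes its inputs as decreases in incidence, which measure how far each treatment lowers incidence from some untreated level. The two scales coincide only under a condition that the article does not state.

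This calculation is the article's only justification for the size of the trial. If the decreases are relative, the difference in incidence that they imply is smaller than the 20 points in the formula, and the power for it is lower than stated. The comparison of effectiveness also feeds the cost-effectiveness ratios (sections 2.9 and 2.14.2), so readers should know what difference the trial can detect.

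**Working it through.** **Inputs from the article.** Proportions 0.60 and 0.40; power 80%; alpha read as 5%; 15% losses; two equal groups (section 2.10 and abstract).

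**Assumed input.** Untreated incidence I0, shown over a range because the article gives none.

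**Step 1: reproduce the 97.** Pooled-variance formula, two-sided 5%, no continuity correction, with p̄ the mean of the two proportions:

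n = [1.960·√(2·p̄·(1−p̄)) + 0.842·√(p1(1−p1) + p2(1−p2))]² / (p1−p2)²

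With p1 = 0.60, p2 = 0.40 and p̄ = 0.50:

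n = [1.960·√0.50 + 0.842·√0.48]² / 0.20² = (1.386 + 0.583)² / 0.04 = 96.9, which rounds up to 97.

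Variants on the same inputs do not give 97: unpooled variance 95, continuity-corrected 107, one-sided 77. The stated figure is therefore the two-sided 5% result with the decreases entered directly as arm proportions.

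**Step 2: reproduce the 114.** 97 / (1 − 0.15) = 114.1, which matches 114. (97 × 1.15 = 111.6 does not.)

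**Step 3: relative reading.** A relative decrease r from I0 leaves an incidence of I0·(1 − r):
- varnish: I0·(1 − 0.60) = 0.4·I0
- sealant: I0·(1 − 0.40) = 0.6·I0
- difference: 0.2·I0

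The difference equals the 20 points in the formula only if I0 = 100%.

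Power = Φ{[|p1−p2|·√n − 1.960·√(2·p̄·(1−p̄))] / √(p1(1−p1) + p2(1−p2))}

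Example at I0 = 60% (24% v 36%, p̄ = 0.30, n = 97): (0.12·√97 − 1.960·√0.42) / √(0.1824 + 0.2304) = (1.182 − 1.270) / 0.642 = −0.137, and Φ(−0.137) = 0.445.

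| Assumed I0 | Varnish v sealant | Power, 97 per arm | Power, 114 per arm | n per arm for 80%, before losses |
|---|---|---|---|---|
| 100% | 40% v 60% | 80% | 86% | 97 |
| 90% | 36% v 54% | 72% | 78% | 119 |
| 70% | 28% v 42% | 53% | 60% | 182 |
| 60% | 24% v 36% | 45% | 51% | 228 |
| 50% | 20% v 30% | 36% | 41% | 294 |
| 30% | 12% v 18% | 21% | 24% | 555 |

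**Step 4: absolute reading.** If the decreases are percentage points, the incidences are I0 − 0.60 and I0 − 0.40, and the difference stays at 20 points. An incidence cannot be negative, so I0 must be at least 60%. Power with 97 per arm is then 94% at I0 = 70% (10% v 30%), 87% at 80% (20% v 40%), 82% at 90% (30% v 50%) and 80% at 100% (40% v 60%).

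**Step 5: what 97 evaluable per arm can detect.** Solving the power formula for the absolute difference that gives 80%: 16.0 points above a lower-arm incidence of 12%, 18.2 above 20%, 19.9 above 36% and 20.0 above 40%.

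**The case against.** The strongest reply is that the loss of power is conditional. Section 2.10 does not say whether the decreases are relative or absolute. On the absolute reading the 20-point difference and at least 80% power stand. The wording may also be loose for expected arm proportions, in which case 97 is simply right. This stands. A reader might infer that the trial is underpowered, but the article does not establish that; it establishes a mismatch of scale that leaves the 80% unsupported as written. Against the reply, a percentage decrease in incidence usually means a relative one, and the absolute reading needs an I0 of at least 60% that the article does not state.

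Second, I0 is assumed. Children at high or moderate caries risk (section 2.2) and an outcome that counts visible enamel change (section 2.8) point towards higher values, so the lowest powers in the table may be pessimistic. This is fair for the size of any shortfall. It does not change the direction: on the relative reading, no I0 below 100% restores 80% at 97 per arm.

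Third, the article does not fix whether incidence is counted per child, tooth or surface. The power figures are child-level because the sample size counts subjects.

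Two further inferences lack support. Nothing in the article says that a non-significant result would be taken as equal effectiveness and settled on cost; the planned ratios use both costs and effects. And the 95% alpha is a slip for 95% confidence, since the calculation itself used 5%.

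**Conclusion.** The point holds as a mismatch between the inputs of the sample size and the primary outcome. The arithmetic is correct for the numbers entered; the fault lies in what those numbers represent. Section 2.10 itself calls them decreases, and the exact reproduction of 97 shows that they went in as arm proportions.

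The size of the consequence depends on two things that the article does not state. If the decreases are relative, power with 97 evaluable children per arm falls from 72% at an assumed I0 of 90% to 21% at 30%. Retaining all 114 still gives only 78% and 24% at those values. If the decreases are absolute and I0 is at least 60%, power is 80% or more. No single corrected power or sample size can be given from the article, and the flat statement that the trial lacks 80% power goes further than the text allows. Confidence is high for the mismatch and conditional for the loss of power.

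**What to change.** Keep 114 per arm and restate section 2.10:

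1. State the assumed untreated 24-month caries incidence.
2. Say whether the 60% and 40% are relative or absolute decreases.
3. Give the expected incidence in each arm that follows from these.
4. Then either replace the 80% with the power those incidences give at 97 evaluable per arm, or say that 97 evaluable per arm gives 80% power for an absolute difference in incidence of about 16 to 20 points (lower-arm incidence 12% to 40%).
5. Replace the alpha of 95% with a two-sided alpha of 5%.

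The cost is the rewording of one section and, if the decreases are relative, a less favourable stated power. No more patients are needed.

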### Recruitment

2.11

The first thing that will be done in this process will be to obtain permission to conduct the study from the corresponding school authorities. For this, it is necessary to deliver a printed protocol to the school addresses of the area; once the study is authorized by the authorities, the following step will be to obtain permission from each of the schools that will participate in the intervention.

The next step is to obtain, through meetings with the parents, authorization for their children to participate in the investigation through the signing of informed consent forms.

Once informed consent has been obtained, the children will be reviewed to identify possible candidates for the study according to the inclusion and exclusion criteria. Once the established sample size has been reached, the participants will be randomly assigned to one of the intervention groups.

### Assignment for each intervention group

2.12

For the randomization process, the total number of candidates will be included in an Excel database; Excel includes a random number function, which will be used in the randomization process.

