### Study design

2.1

This is a randomized experimental design that will be carried out on the FPMs of schoolchildren from public elementary schools in the state of Hidalgo, Mexico. Start date: 2019–03-05.

Hidalgo is one of the 31 states, which, with Mexico City, comprise the 32 Federal Entities of Mexico. It is divided in 84 municipalities and its capital city is *Pachuca de Soto*. Hidalgo is one of the Mexican states that participated in the fluoridated domestic salt program implemented nationally in 1991. Mexico has no water fluoridation program at the national level; however, some states, including parts of Hidalgo, have water with naturally high levels of fluoride. This is not the case in Pachuca, the capital city of Hidalgo.^[27,28]^

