### Trial intervention

2.6

The PFSs to be used in this study have been used for years in other populations. Children will be randomly assigned to either the PFS or varnish group and each subject will remain in their assigned group throughout the study.

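### Minor, nearly free improvement: the allocation makes no use of school although every child is listed beforehand, so the split within schools is left to chance

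*Protocol article*

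**What the plan says.** All of this is in the Protocol article.

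- **Unit.** Section 2.6 randomizes individuals: "Children will be randomly assigned to either the PFS or varnish group".
- **Timing.** Section 2.11 completes recruitment first: "Once the established sample size has been reached, the participants will be randomly assigned to one of the intervention groups".
- **Method.** Section 2.12 is a single sentence. It says that "the total number of candidates will be included in an Excel database" and that "Excel includes a random number function, which will be used in the randomization process". It does not say how the numbers become groups, and it names no block or stratum.
- **Target sizes.** The abstract states: "Participants will be assigned to two treatment groups of 114 each". Section 2.10 reaches the same 114 per group.
- **Setting.** Section 2.2 places the treatments in selected public primary schools in selected municipalities. Section 2.1 notes that some states, "including parts of Hidalgo, have water with naturally high levels of fluoride", and that Pachuca does not. The number of schools is not given.
- **Analysis.** Section 2.14 outlines univariate and then bivariate analysis with non-parametric tests. School is not mentioned.

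**The concern.** Children in one school share a neighbourhood, a water supply and similar access to dental care, so caries risk can plausibly differ between schools. If the list is randomized as one pool, one school may contribute mostly sealant children and another mostly varnish children. Part of the observed arm difference would then reflect which schools fell more heavily into which arm, and a bivariate comparison of arms would not take that out.

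The usual practical obstacle to stratifying is that children enrol one after another. It is absent here, because the whole list exists before anyone is allocated. At stake is some precision, and the credibility of the comparison if the baseline table shows a visible imbalance by school.

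**Working it through.** **1. The plan's own sample size.** Inputs from section 2.10: proportions 0.60 and 0.40, power 80%, and "a power of 80%, and an α of 95%, which gave a sample size of 97 subjects". I read the α as 95% confidence, that is 0.05, and assume a two-sided test.

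n per group = [1.960·√(2·0.5·0.5) + 0.842·√(0.6·0.4 + 0.4·0.6)]² / 0.20² = 96.9, so 97. With 15% loss, 97/0.85 = 114.1, stated as 114. The plan's figures reproduce.

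**2. Does the method give 114 per group?** Two procedures fit the text of 2.12.

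- *Sort the list by random number and cut at 114:* 114/114 with certainty.
- *Independent 50:50 draw per child:* the count in one arm is Binomial(228, 0.5), with SD √228/2 = 7.5 and a 95% range of about 99 to 129. P(exactly 114) = 5.3%.

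Even at 99/129 the power is 85.4% against 86.0% at 114/114. After 15% loss it is 79.3% against 80.0%. The cost is under one percentage point, so group size is not the issue.

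**3. Balance within schools when 114/114 is forced.** The number of schools is my assumption, with equal sizes. The count of one arm in a single school of size m is hypergeometric. The last column is the joint probability over all schools, computed exactly.

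| Assumed schools | Children per school | P(a given school splits 60/40 or worse) | P(at least one school does) |
|---|---|---|---|
| 4 | 57 | 6.6% | 21% |
| 6 | 38 | 21% | 72% |
| 10 | 22 (total 220) | 26% | 94% |

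These describe uneven splits, not error in the result. With many small schools some uneven split is almost certain and matters little overall.

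**4. Effect on the arm difference.** Assume a mean risk of 50%, 114 per arm, and a between-school SD of risk τ. The total variance per child separates as p(1−p) = (average within-school variance) + τ². Balancing on school and analysing by school removes the τ² part.

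- SE without stratification: √(2·0.25/114) = 6.62 percentage points.
- SE with perfect stratification: √(2·(0.25 − τ²)/114).
- SD of the shift in the arm difference due to school imbalance alone: τ·√(2/114).

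| Assumed τ (points) | SE with stratification (points) | Reduction in SE | SD of shift from school imbalance (points) |
|---|---|---|---|
| 5 | 6.59 | 0.5% | 0.7 |
| 10 | 6.49 | 2.0% | 1.3 |
| 15 | 6.32 | 4.6% | 2.0 |

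For comparison, the planned contrast is 60% − 40% = 20 points.

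**5. Does this eat into the planned power?** No. The formula in step 1 uses p(1−p), which by the identity in step 4 already contains τ². The 80% is therefore calculated with unstratified school differences included.

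**The case against.** The strongest reply is that nothing here is an error. Individual randomization without strata is valid and unbiased, chance imbalance by school is ordinary sampling error, and the sample size formula already carries it. All of that stands. It is why this is an improvement and not a defect.

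Three stronger readings are tempting, and the document supports none of them.

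- *The allocation is unrestricted and cannot yield 114 per group.* Section 2.12 does not say unrestricted. Sorting and cutting the complete list fits 2.11 and 2.12 and delivers the sizes in the abstract.
- *School confounds the comparison.* Randomization leaves no systematic link between school and arm. Only chance imbalance is possible.
- *Natural fluoride makes the selected schools differ.* Section 2.1 says that fluoride varies within the state, but nothing says that the chosen schools span high- and low-fluoride areas. The values of τ above are therefore assumptions.

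It can also be said that an article may leave strata and model terms to a fuller protocol or analysis plan. That is fair, and if those documents already provide for school, the point is met. The recommendation does not rest on missing detail, however. It rests on the design that is described, one pooled list completed before allocation, which makes a better method available at almost no cost.

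**Conclusion.** A minor point, worth adopting because it is almost free. As described, the plan randomizes one pooled list from several schools without using school, and the stated bivariate analysis does not account for it. The likely gain from doing so is a reduction of about 0.5% to 5% in the standard error of the arm difference, together with protection against a visible chance imbalance by school. The range rests on an assumed mean risk of 50% and an assumed between-school SD of 5 to 15 points. The split probabilities rest on an assumed 4 to 10 equal schools. The change corrects no bias and restores no lost power, because the plan has neither problem on this account.

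**What to change.** In section 2.12, state the procedure:

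1. Once recruitment is complete, sort the final list by school.
2. Attach one random number to each child and order the children by it within school.
3. Assign one half of each school to sealant and the other half to varnish. Where a school has an odd number, give the extra child to the two arms in alternation from school to school. Since 228 is even, the number of odd-sized schools is even, and the totals stay 114/114.
4. Convert the random numbers to fixed values, because Excel's random functions recalculate, and archive the frozen list before the first treatment.

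In section 2.14, include school as a stratification factor in the caries comparison, for example by a Mantel–Haenszel analysis stratified by school or a school term in a regression model.

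The cost is a few spreadsheet steps and one stratification term. No extra children, visits or staff are needed.

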### Blinding and masking

2.13

In this study, the type of blinding that will be applied will be simple since the participants will not know what type of technology will be used in each individual. To guarantee this, the subjects will not observe the applications that the other participants will receive. This implies that the subjects will pass individually and be isolated from the other subjects during their participation. In addition, a very similar protocol will be carried out for the application, such as prophylaxis, and therefore the participant will not know what type of treatment will be applied.

